# Supervised exercise protocol for lower limbs in subjects with chronic venous disease: an evaluator-blinded, randomized clinical trial

**DOI:** 10.1186/s13063-020-04314-1

**Published:** 2020-05-19

**Keywords:** Exercise, Resistance training, Exercise therapy, Venous insufficiency, Randomized controlled trial, Rehabilitation

## Abstract

**Background:**

Chronic venous insufficiency (CVI) causes pathophysiological changes in the lower-limb muscles, particularly the calf muscles, and limits ankle range of motion (ROM). These changes reduce functional activities and decrease quality of life (QOL). Although several studies have shown the benefits of exercise (strengthening the calf muscles to improve calf-muscle pumping and QOL) in patients with CVI, few studies are randomized controlled trials. This has led to a weak indication of exercise for the treatment of patients with CVI. The aim of this study is to analyze the effects of a supervised exercise program to improve calf-muscle endurance as well as QOL in patients with CVI.

**Methods/design:**

This is an evaluator-blind, randomized clinical trial with an 8-week duration and a follow-up evaluation at week 16. A pilot study with subjects with a CVI diagnosis will be performed to calculate sample size. The participants will be randomly allocated (1:1) into a treatment or a control group (usual care/no intervention). The treatment intervention consists of a bi-weekly supervised exercise program of the lower limbs that will include aerobic training, strengthening and cardiovascular exercises. The participants from both groups will participate in a health education lecture. Primary outcomes are changes in calf-muscle endurance and QOL score. Secondary outcomes are changes in exercise capacity, ankle ROM, electrical muscle activity and cardiac output. The first statistical comparison will be performed after 8 weeks’ intervention.

**Discussion:**

Patients with CVI may have an impaired calf-muscle pump and decreased exercise capacity. A randomized controlled trial evaluating a supervised exercise program should provide much needed information on the management of CVI to promote health and independence.

**Trial registration:**

This study was registered on the Brazilian Clinical Trials Database (REBEC) (RBR-57xtk7). The results will be disseminated at scientific events, presentations, and publications in peer-reviewed journals.

## Background

Chronic venous insufficiency (CVI) is a common health problem and may cause significant morbidity and mortality [1]. It develops when the venous pressure is increased and blood return is impaired. Several mechanisms may result in blood-flow impairment including incompetent valves (superficial or deep veins), perforating veins, venous obstruction or a combination of these mechanisms. This leads to general or local venous hypertension, mainly while standing or ambulating, contributing to macro- or microcirculatory hemodynamic impairments [2] and local tissue ischemia [3]. CVI includes a wide range of clinical signs varying from varicose veins and uncomplicated telangiectasia to venous ulceration [1, 4].

Patients with CVI may develop musculoskeletal changes, mainly in the calf muscles (gastrocnemius and soleus), such as muscle-fiber atrophy [5], leading to abnormal cadence [6] and reductions in muscle strength and function [7]. A decrease in the skeletal-muscle pump worsens venous hypertension, leading to excessive accumulation of fluid and fibrinogen in subcutaneous tissue, which in turn causes edema and/or lipodermatosclerosis, and may lead to venous ulcers [2, 8, 9]. Additionally, ankle-joint movement is decreased [10] and is associated with a higher risk of venous ulcers. Conversely, satisfactory ankle dorsiflexion and effective function of the calf-muscle pump prevents edema and venous ulcers [11].

Effective calf-muscle pumping, even in the presence of valvular dysfunction or venous obstruction, may develop a compensatory mechanism (assisting in venous return) and thereby decrease CVI symptoms. Some studies have shown the benefits of exercise therapy in participants with CVI with an emphasis on strengthening the calf muscles for improved calf-muscle pumping [12–14]. An improvement in the hemodynamic function of calf-muscle pumping (represented by the ejection fraction and residual volume fraction) was described after a supervised lower-limb strengthening and stretching exercise program [13], and after eight consecutive days of isometric strengthening and resistance exercises in the calf muscles [15] for participants with CVI. Other authors [16, 17] have highlighted the importance of progressive resistance exercises and supervised aerobic training to promote ulcer healing and improve cutaneous microvascular reactivity in participants with CVI.

A systematic review [18] focusing on physical exercise for the treatment of CVI without ulcers found only two studies that met the eligibility criteria. Although both concluded that physical exercise led to an increase in venous filling time and ejection fraction, indicating an improvement in venous hemodynamics, the evidence quality was considered very low with a high risk of bias. Considering that resistance training and progressive isometric exercises are routinely prescribed for other cardiovascular diseases (such as peripheral obstructive arterial disease and coronary artery disease) [17] and that evidence-based exercise programs tested in CVI participants remain limited, we aim to assess the efficacy of a supervised exercise program to improve calf-muscle endurance and QOL as well as to asses ankle range of motion (ROM), electrical muscle activity, exercise capacity and cardiac output in participants with CVI. Additionally, we aim to determine whether the possible gains achieved in a supervised training program remain after an unsupervised period.

### Hypotheses

We hypothesize that a supervised lower-limb muscle-training program in participants with CVI will improve calf-muscle endurance and QOL scores.

## Methods/design

This is an evaluator-blinded, randomized controlled superiority trial with two parallel groups, and a 1:1 allocation ratio, with an 8-week intervention period and outcomes measured at baseline, 8 weeks and 16 weeks as a follow-up evaluation. The first statistical comparison will be performed after 8 weeks of intervention.

### Trial design

The evaluations will start in January 2020. After evaluation, participants will be randomly allocated to two evaluator-blinded groups: the treatment group (TG) and the control group (CG). The randomization.com program will be used to randomize the participants and stratification will be performed to ensure balance between the groups within two strata (Clinical, Etiology, Anatomical, Pathophysiology (CEAP) 2 and 3 and CEAP 4 to 6). A separate, blinded researcher will contact the participants by telephone to ensure allocation concealment during screening, consent and initial assessment. A study researcher responsible for implementation will apply the exercise program.

Patients in the TG will perform the exercise program as described in this protocol and will start 1 week after the initial evaluation. The patients in the CG will continue their usual treatments (medication use, compression stockings and medical guidance). After 8 weeks of intervention, the patients will be re-evaluated (using the same initial evaluation questionnaire) by the same blinded evaluator for each group. The primary outcomes will be calf-muscle endurance and QOL and the secondary outcomes will be exercise capacity, ROM electrical muscle activity, and cardiac output. A final reassessment will be performed 8 weeks after the re-evaluation, as shown in Figs. 1 and 2 (Standard Protocol Items: Recommendations for Interventional Trials (SPIRIT) Figure).

**Fig. 1 Fig1:**
[figure not shown]
Trial design

**Fig. 2 Fig2:**
[figure not shown]
Overview of assessment. Standard Protocol Items: Recommendations for Interventional Trials (SPIRIT) Figure showing the schedule of enrollment, interventions and assessment

All participants will receive educational information regarding the disease, as well as the usual care (hygiene and compressive techniques) and treatments to improve symptoms and quality of life (QOL).

### Study setting

The evaluations will be performed at the Pneumocardiovascular Laboratory, and the intervention program will be performed at the Physical Therapy Office, both located in the University Hospital of Natal/RN, Brazil.

### Recruitment

Participants will be recruited at the Medical Clinic of the University Department of Clinical Medicine in the city of Natal/RN, Brazil. This outpatient facility has five physicians specialized in vascular surgery. The inclusion and exclusion criteria will be presented to the physicians personally. The physicians will be asked to refer all participants who meet the inclusion criteria for the study. All the participants will sign the informed consent form which will be explained by the evaluator before the evaluation.

### Participants

Potential participants with stable CVI who meet the eligibility criteria have been recruited from the Vascular Surgery Outpatient Clinic. They have been invited to participate through an informed consent process. The initial evaluation will be performed by a blinded evaluator through a questionnaire that will include socio-demographic data, co-morbidities, time of CVI diagnosis, and detailed clinical and functional information. The disease classification will be based on the CEAP criteria including: clinical manifestations (C), etiological factors (E), anatomic distribution of disease (A) and underlying pathophysiological findings (P) [4]. Ulcer morphological characteristics (if present), ROM, exercise capacity, muscle endurance and parameters related to QOL will also be assessed.

All participants will sign the informed consent form that will be explained before the evaluation. During the functional tests, hemodynamic cardiac parameters (cardiac output, ejection fraction and systolic volume) and bilateral electrical activity of the calf and tibialis anterior muscles will be assessed.

### Eligibility criteria

The inclusion criteria for this study are male and female patients aged between 35 and 69 years, with CVI diagnosed by venous vascular echo-Doppler (VED), with CEAP between 2 and 6, and without peripheral arterial disease (PAD) (ankle-brachial index (ABI) < 0.9) [19]. The exclusion criteria for this study are participants who do not agree to participate, have ulcers > 4 cm in diameter, or clinical signs and/or confirmed diagnosis of infection as well as the patients who already perform any type of self-reported supervised or unsupervised exercise program (whereas exercise is a subset of physical activity that is both regular and structured) [20], are unable to attend physiotherapy sessions twice a week, and/or have co-morbidities incompatible with moderate to intense exercises [21] such as: acute or uncontrolled congestive heart failure, uncontrolled or unstable angina, uncontrolled cardiac dysrhythmia causing hemodynamic symptoms, severe symptomatic aortic stenosis, recent deep venous thrombosis, recent pulmonary embolism, acute pericarditis or myocarditis, dissecting aneurysm (known or suspected), unstable or uncontrolled blood pressure (systolic pressure > 160 mmHg, diastolic pressure > 100 mmHg), acute systemic infection, or uncontrolled diabetes, limiting musculoskeletal diseases, or difficulty in understanding the study activities.

### Blinding

The researcher who will perform the initial and final evaluations will be blinded to the participants’ allocation group. The participants will be instructed not to make any comments regarding group allocation. The evaluator will not have access to the treatment site where the protocol will be performed to reduce the possibility of interfering with the blinding.

## Interventions

### Exercise prescription

The exercise program will consist of (1) aerobic training, (2) strengthening, and (3) unsupervised stretching exercises performed at home. The cardiovascular exercises will be performed using a cycle ergometer and the rubber step. The muscle strengthening will be performed using resistive loads for the calf muscles. The participants will receive a written and illustrated guide for performing active stretching exercises of the calf and tibialis anterior muscles once a day for 20 s (each muscle group) at home 24 h after supervision [22]. The exercise program will last ~ 40 min and will be performed twice a week, for a total of 16 sessions. Heart rate (HR) and blood pressure will be checked at the beginning and end of the training, as well as at the end of each series.
Aerobic training
Cycle ergometer exercise

The perceived fatigue of the participants will be measured using the modified 0–10 BORG scale [23], every 5 min. The participants will warm up for 5 min on the cycle ergometer without a load at the beginning of the protocol. Next, the participants will perform the cardiovascular exercises using the cycle ergometer for 15 min. The load will be adjusted at a setting up to moderate intensity (between 4 and 6 of the modified BORG scale 0–10).
b)Bench step-up exercise

The bench step-up exercise will be performed on a rubber step at a height of 20 cm. The participants will be instructed to walk up and down on steps with one foot at a time using free cadence. They will be instructed to perform the movement as fast as possible for a maximal of 12 repetitions and exercise progression (5 to 10 repetitions) will be weekly increased, according to individual tolerance.

The load during the program execution may be decreased, the rest time increased or the session interrupted if the subject reports very intense perceived fatigue (7 or above, BORG scale), complains of limiting pain, or develops symptoms incompatible with physical activity. The participants will perform only the exercises under supervision of the physiotherapist responsible for the study protocol. The patients showing exercise limitation due to pain, change in medication, undergoing any alternative treatment, or missing three consecutive intervention sessions will be excluded. The data will be included in the records for further analysis even after exclusion. Medical assistance will be provided to any participant who has an injury caused by the study in accordance with resolution 466/12 of the National Health Council.

## Resistance training

To strengthen and increase the endurance of the calf muscles, the patients will perform at 80% of 1 repetition maximum (RM). The submaximal load of 10-RM estimated percentage 80% of 1 RM [24] will be individually calculated based on momentary muscle failure (inability to perform 10 concentric contractions without significant postural change and repetition velocity during changes against a certain resistance) [25]. To calculate the submaximal load of 10 RM, weight will be added until momentary muscle failure of the individual is achieved during the calf-raise exercises. The last load successfully lifted before momentary muscle failure will be used. The calculated load will be used to customize the training level and will be changed according to the patient’s weekly performance. The exercise will consist of three sets of 10 repetitions with a 1-min rest interval. Successive load progression will be made during the program, maintaining the same volume according to the patient’s performance. The exercises during the initial sessions will be performed without any load. The loads will be applied using an adjustable weight-vest according to each patient.

### Health education speeches

All the participants will be invited to attend an educational speech about the disease, risk factors, lifestyle changes and lower-limb care (hygiene, exercises, dressings), as well as the benefits of using compressive techniques. The speeches will be performed (immediately after the first assessment) by a blinded evaluator for each allocation group who will perform the evaluations and reassessments.

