### Data collection, management and analysis

#### Data collection

The baseline and revaluation data will be collected by a trained physical therapist using a protocol for the outcomes related to the questionnaire (VEINES-QOL), demographic data, and CEAP classification. For the physical tests the evaluator will perform a brief orientation, allowing the patient to practice the movement before beginning the test.

A follow-up report will be available to all participants of the IG. It will include evaluation and re-evaluation information for the next medical appointment. The evaluator will refer to the subject’s physician to identify those excluded from the study due to ankle-brachial index (ABI) values below 0.9 [19].

The data will be stored in one of the laboratory computers and double entry will be performed by two study researchers. Access to the data will be limited to the study researchers and any other access must be authorized by the coordinator.

All data collected will be available on the evaluation form and in the proper computer file. Access to these data will be limited only to researchers with prior permission from the study coordinator. The exercise program will be supervised by a physical therapist with expertise in exercise physiology and experience in supervised exercises. All data regarding the treatment protocol will be registered in the subject’s file and attached to the participants’ medical charts.

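### The text ties the blinded evaluator to allocation groups, and the results report goes to one arm only; neither is reconciled with the blinding section

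*Protocol article*

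**What the plan says.** Four places in the protocol article bear on who assesses outcomes and what that person can know.

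- **Blinding.** "The researcher who will perform the initial and final evaluations will be blinded" to allocation. Participants are asked not to talk about their group, and the evaluator is kept away from the place where training is given.
- **Health education speeches.** "All the participants will be invited to attend an educational speech about the disease", straight after the baseline assessment. The speaker is described as acting "by a blinded evaluator for each allocation group who will perform the evaluations and reassessments", so the speaker and the outcome assessor are the same person.
- **Trial design.** "After evaluation, participants will be randomly allocated to two evaluator-blinded groups". At week 8, patients are re-evaluated "by the same blinded evaluator for each group". Concealment is handled as follows: "A separate, blinded researcher will contact the participants by telephone to ensure allocation concealment during screening, consent and initial assessment".
- **Data collection.** "A follow-up report will be available to all participants of the IG". It holds evaluation and re-evaluation results and is meant for the next medical appointment. No date of issue and no author are given. IG is not in the abbreviation list, which has TG and CG. It is read here as the intervention group.

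**The concern.** The title calls the trial evaluator-blinded. The comparison is exercise against usual care, so participants know their arm, and the evaluator's ignorance of it is the main protection for the measured outcomes. Two sections tie that evaluator to groups, and a third creates a document for one group only.

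The outcome at stake is the primary heel-raise count. Under Assessment of calf-muscle endurance, participants are urged to complete as many raises as they can. The test ends on judgements such as repeated failure to reach height, leaning too heavily on the wall, or bending the knees. An evaluator who knows the arm could, without intending it, encourage one arm more or apply these criteria more leniently.

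**Working it through.** There is no figure in the plan to reproduce, so the check is one of text.

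**1. Is the speaker the outcome assessor?** Yes. The Health education speeches section says so directly.

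**2. Reading A: evaluators or talks organised by arm.**
- The evaluator would know, or could work out, the arm at the talk and at reassessment. This conflicts with the Blinding section.
- It also conflicts with the order of events in Trial design. The initial evaluation comes before allocation, so at that point there are no arms by which to assign an evaluator.
- With one evaluator per arm, evaluator and arm could not be separated. Write each evaluator's additive scoring offset as *e* at baseline and *e′* at reassessment, with T and C for the arms. The bias in the between-arm difference in change is

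  (*e′*_T − *e*_T) − (*e′*_C − *e*_C).

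  A constant offset (*e′* = *e* in each arm) cancels. A change in scoring or encouragement between visits that differs by arm does not.

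**3. Reading B: one blinded evaluator serves both arms and gives one common talk before allocation.**
- The talk is offered to everyone, with a single described content.
- It follows the baseline assessment directly, and allocation also comes after that assessment.
- The Blinding section speaks of one evaluator, in the singular, and the disputed phrase itself calls the evaluator blinded.
- On this reading the talk reveals nothing about arm, and there is no conflict.

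**4. Does the text choose between A and B?** No. The timing favours B, but nothing states that the talk precedes allocation. Both the talk and allocation are placed after the first assessment, without an order between them. The by-group wording occurs in two separate sections, so it is hard to dismiss as one slip.

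**5. The report.** Re-evaluation is at week 8 and the final reassessment is 8 weeks later, at 8 + 8 = 16 weeks. A report that contains re-evaluation results cannot exist before week 8. If it is issued between weeks 8 and 16, one arm holds a document that the other lacks while a blinded assessment is still to come. If it is issued after week 16, it can no longer affect any planned assessment. The text allows either.

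**6. Size.** The expression in step 2 needs the shift in scoring at reassessment. A false-positive rate would also need the standard deviation and the number per arm. Sample size leaves both of these to a pilot of eight patients, and the document says nothing about the shift. No size follows.

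**The case against.** The strongest defence is Reading B. A talk common to both arms, given at the baseline visit by someone who does not yet know the allocation, is no breach of blinding. The protocol also has real safeguards: participants are told not to disclose their group, the evaluator is kept from the training site, and a separate blinded researcher makes the telephone contacts. The report is intended for the participant's next medical appointment, and nothing says that the evaluator prepares it or sees who holds one.

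Most of this stands. A reader might infer that the evaluator is unblinded, or that evaluator and arm are confounded by design. The documents do not support either as fact, since both depend on Reading A. A reader might also want to attach an inflated false-positive rate, but that would require an invented scoring shift and an invented sample size.

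The defence does not show that Reading B is what the protocol says. Staff following the two by-group phrases literally could adopt Reading A. The separate researcher's role is described for screening, consent and initial assessment, not for the visits at weeks 8 and 16, where a cue to arm would matter.

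**Conclusion.** The point holds as an unresolved inconsistency in the description of the safeguard that the title claims. The by-group wording, read literally, cannot be reconciled with the Blinding section or with allocation after the initial evaluation. The benign reading is the more likely one but is unstated. The one-arm report is a second, weaker point: it is a possible cue only if it is issued before the week-16 assessment and reaches the evaluator's notice.

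Bias in the heel-raise count follows only if the evaluator learns the arm and this alters encouragement or scoring. Neither step is established, and the size cannot be derived from the document. The correction is still worth making, because the outcome is effort-dependent and judged, and the change costs little.

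**What to change.** 1. In Health education speeches and in Trial design, delete the words that attach the evaluator to a group. State instead that each evaluator assesses participants of both arms, and follows the same participant at baseline, week 8 and week 16.
2. State that the talk is given at the baseline visit before allocation is made or disclosed. Alternatively, have it given by an existing team member who does not assess outcomes. It can stay an individual talk after each first assessment; a joint session for all participants is not needed and would not fit that timing.
3. Give the results report to both arms, after the week-16 assessment, prepared by someone other than the evaluator.

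Items 1 and 2 are changes of wording or, at most, a reassigned task within the present team. Item 3 delays the report for intervention-group participants, so a medical appointment before week 16 would take place without it. It also adds the small work of preparing reports for the control group.
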